### Outcomes

The outcome assessments, conducted in the participants homes by Research Assistants (RA) and Case Managers/RD’s will occur at inclusion (Baseline, *t* = 0) and at the end of the intervention period (Follow-up, *t* = 2). At the beginning of second part of the intervention some outcome assessments will also be conducted in only the Intervention cluster (In between, *t* = 1). It is, however, not obtained by the same person at baseline, in between, and follow-up for practical reasons. However, all will receive the same training in the methods on obtaining outcome assessments by RA ([name]) or RA ([name]). Due to the design of the study it is not possible to blind neither the RA’s nor the Case Managers/RD’s. An overview of the outcome measurements is presented in Table 1 and described in detail below.

**Table 1 Tab1:** Data collection 2 Content in fridge (sufficient, insufficient, empty)

Measure	Time of data collection		
	Baseline *T* = 0	In between *T* = 1	Follow-up *T* = 2
Quality of life by EQ-5D-3 L	X	X	X
Height, meter	X	X	X
Weight, kg	X	X	X
BMI, (kg*kg/m2)	X	X	X
Muscle strength - Chair stand^1^	X	X	X
Satisfaction with food-related life	X	X	X
UCLA Loneliness Scale	X		X
The Short Warwich-Edinburgh Mental Well-being Scale	X		X
General Self Efficacy Scale	X		X
Refrigerator content^2^	X		X
Sociodemographic	X		
Meals-on-wheels (days/w)	X		

^1^Rise from a chair without using the arms in 30 s

^2^Content in fridge (sufficient, insufficient, empty)

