**Methods:**

This cluster randomized controlled study will consist of two clusters of a total of 5 community aged care areas; the intervention cluster, which hold 3 community aged care areas and the control cluster which hold 2 areas. The 130 community-dwelling older adults, receiving meals-on-wheels, will randomly be allocated to either the intervention cluster consisting of 8 weeks of participation in a rehabilitation program led by a Case Manager or the control cluster receiving usual community aged care. The primary outcome will be assessment of data collection (ratio between completed- and non-completed data) and assessment of sample size. The secondary clinical outcomes will be health-related quality of life (EQ-5D-3 L), muscle strength (chair stand), nutritional status (weight/BMI), loneliness (UCLA scale), mental well-being (Warwich-Edinburgh scale), self-efficacy (General Self-Efficacy scale), satisfaction with food-related life (SWFL scale) and refrigerator content.

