The first part, will consist of education of Health Care Staff in the intervention cluster starts immediately after finishing the baseline assessments and consists of a total of one day of education divided into three days, focusing of aspects of food, meals and nutrition to older adults. The education is performed by Bachelor’s Degree Nutritional and Health Educated Professionals that work within The City of Odense. Also included in the first part of the intervention, training of the Care Manager/RDs including learning to use the new developed tool was performed. The Case Managers will be Registered Dieticians (RDs) and will before commencement of the intervention be trained in managing a rehabilitation program focusing on meals. The training will consist of three days. One day as follow-up on the rehabilitation program. Specific topics include; assessment of functional abilities in relation to meals; goal setting by means of Goal Attainment Scaling (GAS) [24], ethical considerations and communication. The training program is developed specifically for the present study in co-operation with teachers from The University of Southern Denmark (SDU) - Master in Rehabilitation.

The effect of the education and training is assessed due to outcomes on an individual level (see below).Second part of the intervention - Rehabilitation program

In the second part of the intervention, the individual participants in the intervention cluster, will be participating in a rehabilitation program involving collaborative goal setting with a Case Manager.

Before contacting the individual participant, the Case Manager/RD will make a review of the participant’s journal in the municipalities system to find out 1) what kind of food from the meals-on-wheels is delivered, 2) if the participant presently is involved in other rehabilitation programs within the municipality, 3) the present health care situation of the participant, and 4) if the participant formerly had any visit from a RD in the municipality. These data will only be used for the rehabilitation program by the Case Manager/RD that is visiting the participant and will not be systematic collected and registered.

The *assessment* will help the participant and the Case Manager/RD to make collaborative evidence-based *goalsetting* to select initial areas for chance of meal activities.

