In the present study, goals will be short-term (i.e. realistic to reach within the intervention period), and a maximum of three goals will be selected for change.

Thus, the Case Managers will encourage participants to involve in these activities.

When *implementing* the activities in relation to meals the Care Manager/RD will plan the intervention interdisciplinary with other professionals within The City of Odense e.g. Occupational Therapist, Physiotherapist, Health Care and Kitchen Staff. A period of eight weeks is chosen for the rehabilitation program in order to get a realistic comparison. This is the minimum amount of time for a Danish municipality rehabilitation program [21]. The intervention is individual and will consist of a minimum of three contacts to the Case Manager/RD in order to *monitor* and *reassess*. After completion of the rehabilitations program a final evaluation will be made.

The participants in the control group will receive usual care in relation to meals; this includes a number (one to seven) hot meals-on-wheels arriving one to three times per week, along with usual support at home.

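### Case Managers who deliver the programme also share the outcome assessments, so only intervention participants can be assessed by their own coach: an avoidable risk of differential bias

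*Protocol article*

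**What the plan says.** **Who measures.** The Outcomes section places the baseline (t=0) and follow-up (t=2) assessments in the home, "conducted in the participants homes by Research Assistants (RA) and Case Managers" (the Case Managers being registered dietitians). Some measures are repeated in the intervention cluster only, at t=1. The section adds: "It is, however, not obtained by the same person at baseline, in between, and follow-up for practical reasons". All assessors get the same training in the methods, and the article states that blinding them is not possible.

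**Who treats.** The abstract contrasts "participation in a rehabilitation program led by a Case Manager or the control cluster receiving usual community aged care". The article describes the rehabilitation phase thus: "the individual participants in the intervention cluster, will be participating in a rehabilitation program involving collaborative goal setting with a Case Manager". The article continues, "Thus, the Case Managers will encourage participants to involve in these activities", and says that the intervention "will consist of a minimum of three contacts to the Case Manager/RD". For controls: "The participants in the control group will receive usual care in relation to meals". No Case Manager is mentioned for them.

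**Other safeguards.** The Blinding section gives the analysis to an external assistant who does not know the allocation. The limitations do not mention that delivery and assessment overlap.

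**The concern.** Lack of blinding and lack of independence are separate problems. The article explains the first. It does not explain why people who deliver the programme should also measure its result.

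Most clinical outcomes are answered at home in front of the assessor (EQ-5D-3L, loneliness, mental well-being, self-efficacy, satisfaction with food-related life) or depend on effort and encouragement (30-second chair stand). A participant who reports to the professional with whom they set and pursued goals has a reason to answer favourably, and that professional has a stake in the answer. Controls have no counterpart to this relationship.

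Three uses of the data are exposed:

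- the between-group comparison, which the Analysis section says the authors want to explore;
- the completeness ratio, which is the primary feasibility outcome;
- the pre-post comparisons that the Trial design section plans in order to separate the two parts of the intervention.

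**Working it through.** The article gives no figure for this point, so the check is mainly a reading of the sections together.

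**Step 1. Possible allocations of assessors at t=2.** The article does not state the split, so each reading is taken in turn.

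- *Case Managers assess intervention participants only.* Assessor role is then partly or wholly aligned with arm.
- *Case Managers assess in both arms.* An intervention participant may be seen by their own coach. A control may be seen by a Case Manager, but never by their own.
- *Case Managers do no t=2 visits.* The follow-up comparison is then not exposed. The text does not say this: the sentence that names the assessors is the one that lists t=0 and t=2.

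On none of these readings can a control participant be assessed by their coach. On the first two, an intervention participant can.

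**Step 2. Do the stated safeguards remove the risk?**

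- Common training standardises technique, not the relationship between coach and client.
- A blinded analyst protects the analysis, not data already collected.
- Using different people at different visits does not keep the treating Case Manager away from t=2. It is given as a practical matter, with no rule by arm or role.

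**Step 3. Completeness.** The Primary outcome section defines feasibility as completed against non-completed or unavailable measures. A familiar Case Manager may obtain a different ratio from a Research Assistant. If role is not recorded, a pooled ratio cannot show this.

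**Step 4. Pre-post comparisons.** Table 1 repeats EQ-5D-3L, weight, height, BMI, chair stand and food satisfaction at t=0, t=1 and t=2. If the assessor role changes between two of these visits, that change falls in the same interval as one part of the intervention and cannot be separated from it without a record of role.

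**Step 5. Illustration of size (the bias is assumed).** Inputs from the Sample size section: an earlier study's EQ-5D-3L follow-up scores of 0.758 (SD 0.222) and 0.534 (SD 0.355), and about 53 per group.

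- Observed difference in that study: 0.758 − 0.534 = 0.224.
- Root-mean-square SD: √[(0.222² + 0.355²)/2] = 0.296.
- Standard error of a difference: 0.296 × √(2/53) = 0.0575.
- With no true effect and an average shift b in the intervention arm, the two-sided 5% rejection probability is 1 − Φ(1.96 − b/SE) + Φ(−1.96 − b/SE).

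| Assumed b | b / 0.224 | False-positive rate |
|---|---|---|
| 0 | 0% | 5% |
| 0.02 | 9% | 6% |
| 0.05 | 22% | 14% |
| 0.10 | 45% | 41% |

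Here b is an average over the whole arm. If half the intervention follow-ups were done by the participant's own coach, an average of 0.05 would need a shift of 0.05/0.5 = 0.10 in those visits. Clustering is ignored.

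**The case against.** **The split is not stated, and staff assignment is operational detail that an article may leave to the full protocol.** This stands in part. A reader might infer that Case Managers assess the intervention arm alone, or that the results are biased. The article supports neither. What it does state is that people who deliver the programme share its assessment, and the point rests on that statement and not on a missing rule.

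**The primary outcome is not a between-arm comparison.** This also stands. A reader might infer that the completeness ratio is necessarily biased. No arm comparison is defined for it, and if the future trial used the same mix of assessors, the pooled ratio would be the relevant one. What remains is that completeness may differ by role, and the future trial would need to know.

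**The 0.224 is not a planned effect.** Correct. The Sample size section reports the two means as an earlier study's result and never names a target difference. The percentages in the table are only a scale, and severity should not be judged from them.

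**It is a pilot, unblinded assessment is disclosed, and some measures are less exposed.** Weight is taken on calibrated scales, and chair height and mode of chair stand are registered. This limits the concern for those outcomes but not for the questionnaires. The second aim still concerns improvement in quality of life and muscle strength against usual care.

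**Conclusion.** The concern holds as a risk of differential bias, not as bias shown. It rests on two stated facts: unblinded Case Managers share the outcome assessments, and Case Managers deliver the programme in the intervention arm, with none described for controls. Together these mean that only intervention participants can be assessed by the person who coached them.

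The outcomes most exposed are the self-reported scales and the chair stand. Effects on completeness and on the pre-post comparisons are possible, not certain. The documents give no basis for estimating the size. The false-positive rates of 6% to 41% depend entirely on assumed average shifts of 0.02 to 0.10, and show only that a modest shift would matter at this sample size.

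This is an avoidable weakness that is cheap to reduce. It is not a flaw that invalidates the pilot.

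**What to change.** In the Outcomes section:

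1. State that no Case Manager assesses a participant they treat.
2. Have the existing Research Assistants do the t=2 visits in both arms where feasible, and otherwise a Case Manager who does not treat that participant.
3. Record the assessor's role at each visit (one data field).

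In the analysis and report:

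4. Present outcomes and completeness by assessor role.
5. List any remaining overlap of delivery and assessment as a limitation. If visits have already been made, steps 4 and 5 still apply wherever role can be recovered.

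**Cost.** Some rescheduling and travel for staff who are already trained. The Implementation section has a Research Assistant obtain consent in the home, without distinction by arm, so follow-up by Research Assistants in both arms is plausible. Staff numbers are not given, so its feasibility must be confirmed. Exchanging clients between Case Managers still leaves an unblinded deliverer as assessor, and is therefore second best. Giving Case Managers equal shares of visits in both arms is not proposed: the intervention cluster is recruited first and the control cluster afterwards, so it would extend their work into a later period at a cost the article does not allow one to judge.

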#### Primary outcome

The choice of assessment tools is carefully selected to include factors found to be associated with nutritional intake in a former study [25] and to emphasize those factors recommended by the Danish National Board of Health to be used to evaluate community-dwelling older adults [26–28].

The feasibility of using the chosen outcome measurements will be assessed by recording the data collection by ratio between completed questionnaires/scales/record charts and non-completed or unavailable questionnaires/scales/record charts, and physical outcome measurements by ration between those participants measured and those that could not be measured.

#### Secondary outcomes

EuroQol-5D-3 L (EQ-5D-3 L) will be used to measure health related quality of life, which is the primary outcome (at *t* = 0, *t* = 1, *t* = 2). EQ-5D-3 L is a standardized instrument for use as a measure of health outcome and is recommended by the Danish National Board of Health [26–28]. The EQ-5D-3 L descriptive system comprises the following 5 dimensions (5D): Mobility, self-care, usual activities, pain/discomfort, and anxiety/depression. Each dimension has 3 levels (3 L): No problems, some problems, extreme problems. The raw score must be converted to an EQ-5D-3 L score ranging from 1.000 to − 0.624 [29]. Permission to use EQ-5D-3 L has been obtained from www.euroqol.org/.

Thirty-second chair-stand, recommended by the Danish National Board of Health [26–28] will be used to measure muscle strength (at *t* = 0, *t* = 1, *t* = 2). Participants are asked to fold their arms across the chest and to stand up and sit down on a chair without pushing off with arms, as many times as possible for 30 s. The arms may be used for assistance or for safety if need [30]. The height of the chair and mode of chair stand will be registered.

Nutritional status will be assessed by means of weight, height, and BMI (at t = 0, t = 1, t = 2). Weight (in kg to the nearest decimal) is measured (with participants wearing light indoor clothes) on calibrated project weights. As measurement of height is often not feasible in this old and frail population with chronic disease, data of height will also be retrieved from self-reported height. BMI is calculated as actual weight in kilograms divided by the square of height in meters.

Loneliness will be measured by a modified UCLA Loneliness Scale, recommended by the Danish National Board of Health [31] (at *t* = 0, *t* = 2). The scale consists of 20 items (11 positive and 9 negative), describing subjective feelings of loneliness, none of which refers specifically to loneliness. Consequently, the scale does not directly measure states that laypeople attribute as loneliness, but rather the scale measures a theoretically defined and scientifically validated understanding of loneliness. The 19 items are rated on a 4-point Likert scale in accordance with the rate of frequency, ranging from never [1] to always [4]. The 20th item in the scale; a question (How many people do you know, in fact, as you would call “my friend / my girlfriend”?), will be converted on a 4-point Likert Scale in accordance with the rate of numbers of friends, from zero friends (1), one to ten friends (2), eleven to forty-nine friends (3), and more than fifty friends (4). As described in Russel DW [32] the items 1, 5, 6, 9, 10, 15, 16, 19 and 20 will be reversed (e.g. 1 = 4, 2 = 3, 3 = 2, 4 = 1). Scores on the scale range from 20 to 80 with higher scores reflecting greater loneliness [33].

Mental well-being will be measured by the short Warwich-Edinburgh Mental Well-being Scale (SWEMWBS) – Danish version 2014 (at *t* = 0, *t* = 2). SWEMWBS is a 7-item scale; each answered on a 1 to 5 Likert scale, with most items representing aspects of psychological and eudemonic well-being, and few covering hedonic well-being or affect. Item scores are summed to produce a total score ranging from a minimum of 7 to a maximum of 49, with higher scores representing higher levels of mental well-being [34–36]. Acceptance of using the SWEMWBS Questionnaire has been obtained from Warwick Medical School, University of Warwick, UK.

Self-efficacy will be measured by The General Self-Efficacy Scale (GSE) (at *t* = 0, *t* = 2). The GSE is a 10-item psychometric scale used to assess optimistic self-beliefs to cope with a variety of difficult demands in life. A typical item is, “Thanks to my resourcefulness, I can handle unforeseen situations.” Possible responses are not at all true (1), hardly true (2), moderately true (3), and exactly true (4), yielding a total score between 10 and 40 with a higher score indicating more self-efficacy [37]. GSE is translated into Danish [38].

The satisfaction with food-related life will be measured by the Satisfaction with Food-related Life (SWFL) scale (at *t* = 0, *t* = 1, *t* = 2). The SWFL, consists of 5 items grouped into a single dimension (e.g. Food 1: Food and meals are positive elements; Food 2: I am generally pleased with my food; Food 3: My life in relation to food and meals is close to ideal; Food 4: With regards to food, the conditions of my life are excellent; Food 5: Food and meals give me satisfaction in daily life.). In each scale, the respondents must indicate their degree of agreement with these statements using a 5-level Likert scale (1 = disagree completely, 5 = agree completely). Each item will be calculated and reported separately and totally [39].

A picture of the participants’ refrigerator will be used to assess the qualitative and quantitative contents of refrigerators (at *t* = 0, *t* = 2). The categories will be “sufficient”, “in-sufficient” (e.g. with old food, according to date or appearance) or “empty” (less than 3 solid food) [40, 41].

For each participant sociodemographic data will be collected; this include age, marital status and yes/no if living alone (at t = 0). Also, data describing numbers of meals delivered by meals-on-wheels on a weekly basis will be collected.

Compliance i.e. use of and participation in possible and suggested activities in relation to meals, number of visits from Dieticians and other staffs involved, plus reasons for canceling of such planned visits and unintended adverse events/possible problems related to the suggested intervention strategies will be recorded during the 8 weeks of intervention period.

After each contact (visit or telephone) with participant following information will be registered by the Case Manager/RD:who were present at the meeting if the contact was a visit,which interdisciplinary contact within the municipality was made afterwards,the time spent on the specific contact,the Case Managers/RD’s judgment (yes/no) if the participants were motivated in the collaboration, andany unintended adverse events/possible problems related to the suggested intervention.

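### Three outcome definitions need correcting: the chair stand has two conflicting definitions, the stated SWEMWBS maximum of 49 is impossible, and BMI has no fixed height per participant

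*Protocol article*

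**What the plan says.** **Chair stand.** Footnote 1 to Table 1 (Outcomes) defines the measure as "Rise from a chair without using the arms in 30 s". The Secondary outcomes text begins the same way, asking participants to "stand up and sit down on a chair without pushing off with arms, as many times as possible for 30 s". It then adds "The arms may be used for assistance or for safety if need", followed by "The height of the chair and mode of chair stand will be registered". The test is done at t = 0, t = 1 and t = 2. Muscle strength is one of the two outcomes named in the second aim (Background).

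**SWEMWBS.** The Secondary outcomes section describes seven items, "each answered on a 1 to 5 Likert scale", which are summed to a total "ranging from a minimum of 7 to a maximum of 49".

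**Height and BMI.** Table 1 schedules height, weight and BMI at all three time points, with t = 1 in the intervention cluster only. On the source of height, the text says that "data of height will also be retrieved from self-reported height", and gives as its reason that direct measurement often cannot be done in such frail participants. BMI is weight divided by height squared. The Outcomes section states that the assessor is not the same person at each visit, that all assessors receive the same training, and that none can be blinded.

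**Feasibility.** For physical measures, the Primary outcome section sets the number of participants who were measured against the number who could not be.

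**The concern.** Each measure is meant to give one number per participant per visit, and the Analysis section compares changes in such numbers within and between groups. For the chair stand, two participants with the same performance can be scored differently depending on which definition the assessor or analyst follows. A participant who needs the arms has no valid unassisted stand under Table 1 but has a count under the text. That affects the muscle-strength outcome. It also affects the primary outcome, because the same participant can fall on either side of the measured/not measured ratio.

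The SWEMWBS maximum contradicts the item count and item scale given with it. A reader who judges a score or an effect against the printed range would use the wrong scale.

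For BMI, adult height should not change over an eight-week program, so any visit-to-visit difference in recorded height is error that passes straight into BMI change.

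The trial exists to show whether these measures are usable in a definitive trial, so an unclear definition here would carry forward.

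**Working it through.** **1. SWEMWBS range.** Inputs, from Secondary outcomes: 7 items, each scored 1 to 5, summed.
- Minimum = 7 × 1 = 7, which agrees with the stated minimum.
- Maximum = 7 × 5 = 35. The stated 49 is 14 points too high.
- A total of 49 would need a top item score of 49 / 7 = 7, or 49 / 5 = 9.8 items. Neither fits the description.
- The same formula reproduces the article's other ranges: General Self-Efficacy, 10 items scored 1 to 4, gives 10 to 40; UCLA, 20 items scored 1 to 4, gives 20 to 80.
- The stated span is 49 − 7 = 42 and the true span is 35 − 7 = 28, so the printed scale is 42 / 28 = 1.5 times too wide.

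**2. Chair stand.** No arithmetic in the plan applies, so the passages are set side by side.
- Table 1: no arms.
- Text, main instruction: no pushing off with the arms.
- Text, next sentence: arms allowed for assistance or safety.
- Text, following sentence: chair height and mode are recorded.

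The record therefore allows assisted and unassisted tests to be told apart. No passage says which count is the outcome, how a participant whose mode changes between visits enters the change score, or whether an assisted test counts as measured. An invented example shows why the rule matters. A participant does 8 stands with arms at baseline and 5 without arms at follow-up. Taking the count regardless of mode, the change is 5 − 8 = −3. Taking the unassisted count with 0 when arms are needed, it is 5 − 0 = +5. The sign depends on the definition chosen.

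**3. BMI.** Formula: weight / height². The article gives no discrepancy between recorded heights, so 1 to 5 cm is assumed, at an assumed 70 kg and 1.65 m.
- Reference: 70 / 1.65² = 25.71 kg/m².
- Recorded height 1 cm greater: 70 / 1.66² = 25.40, a shift of −0.31.
- 2 cm greater: −0.61. 3 cm greater: −0.91.
- 5 cm greater: 70 / 1.70² = 24.22, a shift of −1.49.

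In relative terms this is 1.2% to 5.8% of BMI with no change in weight. At 1.65 m, 1 kg of real weight change moves BMI by 1 / 1.65² = 0.37, so these shifts equal about 0.31 × 1.65² = 0.8 kg to 1.49 × 1.65² = 4.1 kg. Across 55 to 85 kg and 1.55 to 1.75 m, the shift runs from −0.20 to −2.18 kg/m². If one height is kept per person, it is zero.

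**The case against.** Table 1 is introduced as an overview with details to follow, so its footnote may be shorthand for the fuller rule in the text. The text also records mode and chair height, which are the data needed to separate the two kinds of test. That much stands: the information will exist. But recording the mode does not decide which count is the outcome or who counts as measured. A reader might infer that assisted and unassisted counts will be pooled in one variable; no passage says so.

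On SWEMWBS, the scoring rule is a plain sum, and valid item responses cannot exceed 35 whatever maximum is printed. This stands. A reader might infer that totals of 36 to 49 would pass a range check, or that scores would be rescaled to 49, but the article describes neither.

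On BMI, a reader might infer that measured and self-reported heights are mixed within a person across visits. The article does not say this; its wording fits equally well with collecting both at each visit, and a precedence rule may sit in a fuller document. Weight is measured on calibrated scales and is an outcome in its own right. This also stands. What remains is that the article itself schedules height up to three times, with changing assessors and two sources, although a single value would do.

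The sample size rests on EQ-5D-3L and is not touched by any of the three.

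**Conclusion.** The point holds as a need to correct three definitions. It does not support the stronger claim that the plan distorts three clinical outcomes.
- **Chair stand:** a real conflict between Table 1 and the text, and the most important of the three. It concerns an outcome named in the second aim and the count of participants measured in the primary outcome. Its numerical size cannot be given, because the article does not say how many participants would need their arms.
- **SWEMWBS:** a certain error, 49 where the article's own inputs give 35. Summed scores are unaffected.
- **BMI:** an avoidable source of error, not a demonstrated one. Its size, about 0.3 to 1.5 kg/m² per affected participant, rests on the assumed 1 to 5 cm discrepancy at 70 kg and 1.65 m, and on recorded height differing between visits at all.

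**What to change.** **Chair stand:** reconcile Table 1 footnote 1 with the Secondary outcomes text. Use the recorded mode to analyse two separate variables: the unassisted count (0 if arms are needed) and the arms-assisted count. State in the Primary outcome section which of them counts as measured for the feasibility ratio. This concerns scoring only and does not question whether arms may be used for safety. The cost is some zeros in the unassisted score; reporting the assisted count beside it keeps that information.

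**SWEMWBS:** change the stated maximum from 49 to 35.

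**BMI:** fix one height per participant at baseline, record whether it was measured or self-reported, and use it for BMI at every visit. Rely on measured weight change to assess change in nutritional status. In the same edit, correct the BMI unit in Table 1, printed as kg*kg/m2, to match the formula in the text.

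The total cost is a few sentences in the protocol and matching entries in the data dictionary. No new data are needed, and later height measurements can be dropped.
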